### Data Management and Monitoring

All required information according to this protocol will be recorded on a paper-based case report form. After the last visit, data will be entered in a password-protected and validated relational database (SQL Server 2008 Express). After the last patient’s last visit, database will be soft-locked. A monitoring will be performed on 100% of data necessary to evaluate the primary end point. Of the remaining data, 20% are randomly selected. Finally, the database will be closed and made available for statistical analysis.

### Statistical Analysis

The included scores use different numbers of nutritional risk classes. To compare the scores, evaluation of the primary end point patients will be dichotomized by each nutritional assessment score as “at risk” or “not at risk” using the respective highest nutritional risk determined by each score (Table 1). Further, patients will be dichotomized whether they had at least one major complication (Clavien-Dindo III-V) or not. Hence, for every nutritional assessment score, a contingency table will be created (Figure 1). Positive predictive value, specificity, sensitivity, and c-index will be calculated. Association between every nutritional assessment score and major complication will be expressed as odds ratio with 95% confidence interval. Univariable significance of association will be tested with a chi-square test without Yate’s correction at a level of significance of 5%. A multivariable logistic regression model will be used for evaluation of primary end point at a level of significance of 5%. Covariates will be age (years) and operation time (minutes). Factors will be malignancy; gender; laparoscopy; intraoperative radiotherapy; resection of vessels (portal vein, superior mesenteric artery, or vein); inclusion in an interventional trial; American Society of Anaesthesiologists (ASA) physical status classification system; prior upper gastrointestinal surgery; pancreatic surgery associated risks (amylase in drainage >5000 IE/U on POD 1, biliary stent); and preoperative serum albumin level less than 35 g/L. Subgroup analysis will be performed separately for different types of pancreatic resections and different nutritional risk classes will be determined by each score (Table 1).

Secondary end points will be analyzed descriptively by tabulation of the measures of the empirical distributions. According to the level of the variables, means, SDs, medians, 1st and 3rd quartiles, minimum and maximum, or absolute and relative frequencies will be reported, respectively. Descriptive *P* values of the corresponding statistical tests and associated 95% confidence intervals will be given. Statistical analysis will be performed with program R [43].

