**Methods:**

All patients scheduled to receive elective pancreatic surgery at the University Hospital of Heidelberg will be screened for eligibility. Preoperatively, 12 nutritional assessment scores will be collected and patients will be assigned either at risk or not at risk for malnutrition. The postoperative course will be followed prospectively and complications according to the Clavien-Dindo classification will be recorded. The prognostic value for complications will be evaluated for every score in a univariable and multivariable analysis corrected for known risk factors in pancreatic surgery.

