### Planned Study Conduct and Trial Visits

All patients visiting the Department of General, Visceral and Transplantation Surgery at the University Hospital of Heidelberg and scheduled to receive elective operations will be screened. Eligible patients will be consecutively informed about the study purpose and conduct. After giving a written informed consent, patients will be questioned and examined (Visit 1) according to the investigated nutritional assessment scores (Table 2). Further, other known risk factors for postoperative complications will be noted [32,33]. If the operation is delayed for any reason, patients will be re-evaluated as long as preoperative data from questionnaires are not older than 36 hours at the time of actual operation.

**Table 2 table2:** Flowchart of the NURIMAS trial-course of examinations.

Visit	1	2	3	4
	Preoperative	POD 3-7	POD 10-14	Discharge or POD 30
Eligibility	X			
Informed consent	X			
Baseline data	X			
Nutritional scores	X			
Laboratory analyses	X	x	x	x
Assessment of surgical procedure		x		
Assessment of complications		x	x	x
Serious adverse events		x	x	x
Secondary end points		x	x	x

After the operation, the clinical course will be followed prospectively. Therefore, 3 planned visits will be performed. The first visit will be performed on postoperative days (PODs) 3-7, the second visit on PODs 10-14, and the last visit on the day of discharge or not later than POD 30. During these visits, complications according to Textbox 2 [34-41] will be assessed. Every postoperative complication will be rated according to the validated classification by Clavien-Dindo [42]. Further, on postoperative visits, the status of secondary end points will be evaluated.

Assessed postoperative complications.• Postoperative pancreatic fistula [34]• Bile leak [35]• Postpancreatectomy hemorrhage [36]• Delayed gastric emptying [37]• Surgical site infection [38]• Other infections and sepsis [39]• Chylous ascites (triglycerides in drainage) [40]• Serious adverse event [41]

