## Discussion

The NURIMAS trial is a monocentric, prospective, observational trial aiming to find the most suitable clinical nutritional assessment score to predict major postoperative complications associated with malnutrition. Thus, an important lack of knowledge in preoperative risk assessment in patients undergoing pancreatic surgery will be worked-off. Upon this knowledge, further trials can rely on a validated nutritional risk and evaluate the benefit of nutritional interventions potentially preventing postoperative complications.

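### The multivariable model for the primary end point adjusts preoperative nutritional scores for intraoperative variables and POD-1 drain amylase, so its odds ratio is not the association available before surgery

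*Protocol article*

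**What the plan says.** The Abstract fixes the timing of the exposure: "Preoperatively, 12 nutritional assessment scores will be collected". Aim of the Trial describes the purpose as prediction of postoperative complications, and the Discussion places the work as closing a "lack of knowledge in preoperative risk assessment in patients undergoing pancreatic surgery".

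The Statistical Analysis section dichotomizes the outcome as "at least one major complication (Clavien-Dindo III-V) or not". It then says: "A multivariable logistic regression model will be used for evaluation of primary end point at a level of significance of 5" percent. The listed terms include:

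- "Covariates will be age (years) and operation time (minutes");
- "laparoscopy; intraoperative radiotherapy; resection of vessels (portal vein, superior mesenteric artery, or vein");
- "pancreatic surgery associated risks (amylase in drainage >5000 IE/U on POD 1, biliary stent").

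Minimizing Other Bias gives control of confounding as the reason for these terms. Under Planned Study Conduct and Trial Visits, the first complication in Textbox 2 is "Postoperative pancreatic fistula [34]". Every complication is graded by Clavien-Dindo, and follow-up runs to discharge or at the latest POD 30.

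The article describes no second adjusted model restricted to preoperative variables.

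**The concern.** A confounder of a preoperative score has to be in place before the score is taken, or stand in for something that was. Operation time, intraoperative radiotherapy and vessel resection become known during the operation, and drain amylase a day after it. Relative to the score they may be:

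- mediators, which carry part of the risk that the score marks;
- early manifestations of the outcome;
- at best, proxies for preoperative properties that were not measured.

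In the first two cases, adjustment removes association that the trial wants to measure. It can also open a non-causal path where an unmeasured factor drives both the adjusted variable and the complication.

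Amylase is the sharpest case, because a fistula graded III to V is itself an outcome event. The fitted OR then tells whether the score adds anything once the course of the operation and the POD-1 drain value are known. Nobody can ask that before surgery. It also serves poorly the later nutritional intervention trials named in the Discussion, because harm acting through fistula would be partly adjusted away.

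**Working it through.** **Step 1: timing of the terms, from the article's own list**

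| Term | When known |
|---|---|
| Age, gender, ASA, prior upper gastrointestinal surgery, preoperative albumin | Before surgery |
| Biliary stent | Not dated as postoperative; nothing shows it to be post-baseline |
| Inclusion in an interventional trial | Not dated; treated here as known before surgery |
| Malignancy, laparoscopy | Can be known or planned before surgery; the article does not say which version is recorded |
| Operation time, intraoperative radiotherapy, vessel resection | During surgery |
| Drain amylase | POD 1, within postoperative follow-up |

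Four terms clearly arise after the score.

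**Step 2: how far adjustment could move the OR**

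The article has no figure to reproduce here. It gives no complication rate, no relation between score and amylase, and none between amylase and complications. The following inputs are all assumptions: 25% major complications overall, 30% of patients at risk, OR of the score given amylase 1.50, and OR of high amylase for a complication 2, 4 or 8. The prevalence of high amylase is p₁ in at-risk patients and p₀ in the others.

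With expit(t) = 1/(1 + e^(−t)) and M the amylase OR, the group risks are:

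- at risk: r₁ = p₁·expit(a + ln 1.5 + ln M) + (1 − p₁)·expit(a + ln 1.5)
- not at risk: r₀ = p₀·expit(a + ln M) + (1 − p₀)·expit(a)

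The intercept a is solved from 0.30·r₁ + 0.70·r₀ = 0.25. The total OR is [r₁/(1 − r₁)] / [r₀/(1 − r₀)].

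Worked case: p₁ = 30%, p₀ = 15%, M = 8.

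- a = −1.772. Risks for low and high amylase are 0.203 and 0.671 (at risk), 0.145 and 0.576 (not at risk).
- r₁ = 0.30 × 0.671 + 0.70 × 0.203 = 0.3435
- r₀ = 0.15 × 0.576 + 0.85 × 0.145 = 0.2099 (from unrounded risks)
- Check: 0.30 × 0.3435 + 0.70 × 0.2099 = 0.250
- Total OR = (0.3435/0.6565) / (0.2099/0.7901) = 1.97, against 1.50 adjusted.

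All cases (adjusted OR 1.50 throughout):

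| High amylase, at risk vs not | M = 2 | M = 4 | M = 8 |
|---|---|---|---|
| 30% vs 15% | 1.66 | 1.83 | 1.97 |
| 12% vs 25% | 1.35 | 1.19 | 1.03 |
| 20% vs 20% | 1.49 | 1.46 | 1.40 |
| 22% vs 18% | 1.53 | 1.55 | 1.54 |

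The third row shows non-collapsibility alone: a conditional OR differs from a marginal one even when score and amylase are unrelated. That part is not bias. The fourth row shows that a weak link leaves little difference.

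**Step 3: a second set of assumptions**

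Take 30% at risk and, at the reference level, 15% high amylase and 20% complications. With a score-amylase OR of 2 and an amylase-complication OR of 4, a total OR of 1.72 becomes 1.50 after adjustment. If the score acts only through amylase, a total OR of 1.19 becomes 1.00. With an inverse score-amylase OR of 0.5, 1.32 becomes 1.50. The pattern is the same as in Step 2.

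**Step 4: does the choice of best score depend on it?**

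Outcome Measures selects the score with the highest lower 95% confidence bound of the OR and does not say crude or adjusted. Statistical Analysis attaches the OR with its interval to the association of each score with major complication, just after the contingency tables, and the Figure 1 caption ties the primary end point to such a table. The same section then assigns the multivariable model to the primary end point. Both readings are open.

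**The case against.** The strongest reply is that preoperative prognostic value is reported anyway. Crude ORs, sensitivity, specificity, positive predictive value and c-index use no post-baseline variable. The Abstract describes the multivariable analysis as correcting for known risk factors, which is a different and legitimate question. This stands in part: the adjusted OR misleads only if read as the association available before surgery. But the article assigns the model to the primary end point and defends it as confounding control, and that defence does not fit the four terms.

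It may also be said that reading drain amylase as an early sign of fistula is clinical reasoning from outside the article, which calls it a risk, and that only fistulas graded III to V enter the outcome. Both are true. The timing argument needs neither. If amylase merely stands in for a preoperative property of the gland, part of the adjustment would be reasonable.

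A reader might go further and infer any of the following, which the article does not support:

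- **The wrong score will be chosen.** This follows only if the adjusted OR is the selector, which is not settled.
- **Albumin must also come out.** It is preoperative. Keeping it asks whether a score adds to albumin, which is a defensible question.
- **Resection type has been overlooked.** It is not in the main model, but separate subgroup analyses by type of resection are planned.

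**Conclusion.** The point holds for operation time, intraoperative radiotherapy, vessel resection and POD-1 drain amylase. With these terms in the model, the adjusted OR does not estimate the preoperative prognostic association that the trial states as its aim.

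Neither size nor direction can be taken from the article. With an adjusted OR of 1.50, the assumed cases give total ORs from 1.03 to 1.97. The difference is small for a score with little or no relation to amylase. These figures rest wholly on the assumed inputs and cover amylase alone.

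Because the shift depends on each score's relation to these variables, it could differ between the 12 scores and alter their order, but only if the adjusted OR ranks them. The crude measures are sound on this point. The plan should be changed, but the matter does not invalidate the trial.

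**What to change.** 1. Limit the primary adjusted model to the listed variables known before incision: age, gender, ASA, prior upper gastrointestinal surgery, biliary stent and inclusion in an interventional trial. Add malignancy and laparoscopy as known or planned preoperatively, where that is recorded. Preoperative albumin may stay.
2. Move operation time, vessel resection, intraoperative radiotherapy and POD-1 drain amylase to a sensitivity model that is labelled as such and uses the full list.
3. State whether the crude or the adjusted OR ranks the scores.

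Make the change before the database is closed, since choosing between models after seeing results would weaken the protection against selective reporting that the article claims.

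The cost is mainly wording, because the model uses variables already listed. Two limits remain. The article does not show that the planned approach or a preoperative diagnosis of malignancy is recorded; Table 2 places assessment of the surgical procedure at the POD 3-7 visit. The primary model will also leave somewhat more outcome variation unexplained.

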**Figure 1 figure1:**
[figure not shown]
Contingency table for calculation of primary study endpoint for the prognostic value of every nutritional assessment score.

### Methods for Minimizing Bias

#### Minimizing Selection Bias

All patients will be consecutively screened and if found to be eligible, informed consent will be obtained in the single-arm study. Number of screened, included, and analyzed patients will be reported and differences will be explained.

#### Minimizing Performance and Detection Bias

Preoperative data capturing and outcome assessment will be performed by 2 different investigators. Statistical analysis will be performed after closure of database.

#### Minimizing Attrition Bias

Statistical measurements such as imputation will be taken to minimize risk of bias due to incomplete outcome data [44]. The trial will be reported according to the Standards for Reporting of Diagnostic Accuracy (STARD) statement [45]. The trial is registered with Deutsches Register Klinischer Studien (DRKS00006340). To avoid the risk of selective reporting, the trial protocol with full information about end points and profound explanation of planned statistical analysis is hereby published according to the Standard Protocol Items: Recommendations for Interventional Trials (SPIRIT) statement where appropriate [46]. Report on cost issues and validation of the ESPEN criteria for malnutrition is planned separately.

#### Minimizing Other Bias

Any financial relationship or any conflict of interest that could inappropriately influence the work within this project will be stated explicitly. Confounding will be minimized by inclusion of covariates and factors in the statistical analysis of the primary end point as mentioned in the “Statistical Analysis” section.

### Ethics and Informed Consent

The NURIMAS Pancreas trial is conducted in accordance with the Declaration of Helsinki in its actual version [47]. According to the professional code for physicians in Germany (§15 BOÄ), the trial protocol was reviewed and approved by the Ethics Committee of the medical faculty of the University of Heidelberg.

Before inclusion in the NURIMAS Pancreas trial, patients will be informed both orally and in writing about all relevant aspects of the trial (eg, the aims, methods, the anticipated benefits, potential risks of the study, and the discomfort it may entail). The patients’ free decision to participate will be documented by signature on the informed consent form. All patient-related information is subject to medical confidentiality and to the Federal Data Protection Act. Pseudonymized data transfer will be performed. Third parties will not have any insight into original data.

## Results

Final data analysis is expected to be completed during Spring 2016.

## Discussion

The NURIMAS trial is a monocentric, prospective, observational trial aiming to find the most suitable clinical nutritional assessment score to predict major postoperative complications associated with malnutrition. Thus, an important lack of knowledge in preoperative risk assessment in patients undergoing pancreatic surgery will be worked-off. Upon this knowledge, further trials can rely on a validated nutritional risk and evaluate the benefit of nutritional interventions potentially preventing postoperative complications.

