**Conclusions:**

The NURIMAS Pancreas trial is a monocentric, prospective, observational trial aiming to find the most predictive clinical nutritional assessment score for postoperative complications. Using the results of this protocol as a knowledge base, it is possible to conduct nutritional risk-guided intervention trials to prevent postoperative complications in the pancreatic surgical population.

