### Diagnostic Intervention (Nutritional Assessment Scores)

Based on the most recent systematic review about existing nutritional assessment scores by Van Bokhorst-de van der Schueren [12], 11 scores have been selected that are in use in surgical patient populations [18-27]. Recently, the European Society of Clinical Nutrition and Metabolism (ESPEN) published a new consensus definition of malnutrition, the ESPEN malnutrition criteria [28]. Table 1 presents a summary of the 12 nutritional assessment scores that will be evaluated.

**Table 1 table1:** Nutritional assessment scores.

Name	Classification for nutritional risk^a^
Nutritional Risk Index [18]	Normal/mild/moderate/severe
Nutritional Risk Screening Score and Revised Version [19,26]	Low/ moderate/high
Subjective Global Assessment [20]	No/ moderate/severe
Malnutrition Universal Screening Tool [21]	Low/ medium/high
Mini-Nutritional Assessment and Revised Version [22,27]	Normal/ at risk/malnourished
Short Nutritional Assessment Questionnaire [23]	Low/ moderate/severe
Imperial Nutritional Screening System I [24]	Not at risk/at risk
Imperial Nutritional Screening System II [24]	Green/amber/red
Nutritional Risk Classification [25]	Low/at risk
ESPEN Malnutrition Criteria [28]	Normal/malnourished

^a^The highest class for nutritional risk determined by the scores will be used as the study end point “at risk for malnutrition” for statistical evaluation.

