### Outcome Measures

The primary end point is postoperative morbidity and mortality. The most suitable score is defined as the score with the highest association of malnutrition and postoperative complication expressed as the highest lower bound of the 95% confidence interval of odds ratio.

Secondary end points are length of hospital stay, length of stay in intensive care unit, comprehensive complication index [29], place of discharge (discharge to home or discharge to rehabilitation or care facility), necessity of postoperative parenteral or enteral nutrition, and impact of malnutrition as diagnosis on hospital costs and Diagnosis Related Group (DRG) case cost.

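### The Discussion calls the chosen score validated, but it is the best of 12 picked and measured in the same 260 patients, so its reported performance is biased upward

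*Protocol article*

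**What the plan says.** All references are to the Protocol article.

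- **Candidates** (Diagnostic Intervention): "Table 1 presents a summary of the 12 nutritional assessment scores that will be evaluated". All are existing instruments, and for each the class that counts as at risk is fixed in Table 1.
- **Choice** (Outcome Measures): "The most suitable score is defined as the score with the highest association of malnutrition and postoperative complication". The yardstick is each score's lower 95% limit for the odds ratio, and the score whose limit lies highest wins.
- **Estimates** (Statistical Analysis): "Association between every nutritional assessment score and major complication will be expressed as odds ratio with 95% confidence interval". In addition, "Positive predictive value, specificity, sensitivity, and c-index will be calculated". These come from the cohort that decides the winner: 260 patients, one centre, one arm.
- **Protection against bias** (Methods for Minimizing Bias): selection of patients, performance and detection, attrition, selective reporting and confounding are covered. Optimism from taking the best of several scores is not.
- **Use of the result**: the Discussion says "further trials can rely on a validated nutritional risk and evaluate the benefit of nutritional interventions potentially preventing postoperative complications". The abstract's Conclusions say that on this basis "it is possible to conduct nutritional risk-guided intervention trials to prevent postoperative complications in the pancreatic surgical population".

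**The concern.** A score that wins because its estimate came out highest has, on average, an estimate above its true value. Its confidence interval covers the truth less often than stated. Ranking on the lower limit changes which scores are favoured but does not remove this, since the lower limit moves with the same random error as the estimate.

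The Discussion then gives the selected score a property that the design cannot give it. Validation of the winner would need data that played no part in choosing it, and there are none here. At stake are the size of the effect published for the winner and the weight that later work may put on it. A winner is also named when no score predicts complications.

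**Working it through.** **The plan's own figures.** The article gives no expected odds ratio for the winner and no estimate of optimism, so there is nothing of that kind to reproduce. Its only relevant number is N = 260, which rests on the precision of sensitivity and specificity (Trial Site and Sample Size Calculation). With 0.05 read as a half-width, 1.96² × 0.95 × 0.05 / 0.05² = 73, and 73 / 0.30 gives 244 for specificity. The stated 260 is somewhat larger and adequate for that aim. It says nothing about choosing among 12 scores, and the gap between 244 and 260 plays no part in this point.

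**Inputs.** From the article: N = 260, 12 scores, highest lower 95% limit wins. Not in the article and therefore assumed: the major complication rate, the share each score flags, the true odds ratios and the correlation between scores.

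**Hand check, no score predictive.** Assume 30% events and 30% flagged. The expected cells are 260 × 0.09 = 23.4, 260 × 0.21 = 54.6 (twice) and 260 × 0.49 = 127.4.

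- SE(log OR) = √(1/23.4 + 2/54.6 + 1/127.4) = 0.295.
- The expected maximum of 12 independent standard normal values is 1.629, so the winner's odds ratio is about exp(1.629 × 0.295) = 1.62 when the truth is 1. Simulation gives 1.61.
- With latent correlation 0.5, two yes/no scores each flagging 30% correlate at 0.318. Then exp(1.629 × 0.295 × √(1 − 0.318)) = 1.49. Simulation gives 1.48.
- One score's lower limit exceeds 1 by chance in 2.5% of trials. For the best of 12 independent scores this becomes 1 − 0.975¹² = 26%.

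**Simulation A.** 260 patients, 30% events, 12 scores flagging 5–40%, unadjusted odds ratios with Wald limits, 4,000 trials per row. Means are geometric.

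| Latent correlation | No score predictive: winner's OR | Lower limit above 1 | Similar scores: true → reported OR | Inflation |
|---|---|---|---|---|
| 0.3 | 1.67 | 25% | 1.33 → 2.24 | 1.68 |
| 0.5 | 1.60 | 21% | 1.44 → 2.34 | 1.63 |
| 0.7 | 1.53 | 19% | 1.55 → 2.38 | 1.54 |

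Repeat runs of the no-prediction case ranged over 1.52–1.69 and 18–26%. With one clearly best score, the reported odds ratio was about 2.8–3.0 against a true 2.4–2.6, roughly 1.1–1.2 fold. The largest ratio in a smaller run of 400 trials was 3.02 / 2.39 = 1.26.

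**Simulation B.** Wider assumptions: for equally good scores, events 20–40%, 30% flagged and latent correlation 0–0.9; for the other two rows, events 30% and latent correlation 0.3–0.7.

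| Truth | OR inflation | c-index optimism | Coverage of the 95% interval |
|---|---|---|---|
| 12 equally good scores | 1.27–1.71 | +0.025 to +0.062 | 71–89% |
| True ORs from 1 to 3, one clearly best | 1.10–1.20 | +0.010 to +0.019 | 91–94% |
| One prespecified score, no selection | about 1.00 | about 0 | 95–96% |

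Here the c-index of a dichotomised score is (sensitivity + specificity) / 2. The last row shows that the bias comes from the choice and not from the estimator.

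**Does a bootstrap of the choice help?** With no predictive score, the adjusted odds ratio was 1.09–1.16 (truth 1.00). With similar scores it was 1.56–1.74 (truth 1.33–1.53), so it under-corrects. With one dominant score it was about 2.25–2.3 (truth about 2.55), so it over-corrects.

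**The case against.** The strongest reply is that these are published scores with cut-offs fixed before the data, and no weights are fitted for the contingency tables. For each score singly, the cohort is an independent test in pancreatic surgery. That stands. A reader might infer that the study validates nothing, and the documents do not support so strong a reading. Results are also planned for every score, so the full spread can be reported. This helps the reader but does not correct the winner's figures.

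Second, the article is condensed and no analysis plan is shown. Optimism correction may be specified there, so its absence from the article is not in itself the fault, and one should not infer that no correction exists. What stands on the page is the claim of validation attached to a best-of-12 result. An internal correction would not make that claim true.

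Third, the size depends on inputs that the article does not give. It would be tempting to say that the winner's apparent value is mostly selection. That is so only if the scores are similar and weak; with one clearly superior score the inflation is modest.

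Fourth, a reader might infer that later intervention trials will be too small. The article says only that they can build on this knowledge, not that they will take this odds ratio or event rate as a planning value. That consequence is possible but not documented.

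**Conclusion.** The point holds in this form: the winner's odds ratio, c-index and predictive values, reported as the article describes, are biased upward, and calling the selected score validated goes beyond the design. The direction was the same in every scenario with selection.

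The size is conditional. Under 30% events and 12 correlated scores flagging 5–40%, the odds ratio is inflated about 1.1–1.2 fold with one clear best score, and about 1.5–1.7 fold when scores are similar or none predicts. In the last case the winner's lower limit exceeds 1 in about 18–25% of trials, against 2.5% for a single score. Very strong correlation between scores lowers these figures; at latent correlation 0.9, with 30% events and 30% flagged, the inflation is about 1.29 fold.

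The calculations rank on the unadjusted odds ratio, since the article does not say whether the unadjusted or the adjusted one decides. The same mechanism applies to adjusted estimates, but its size there was not computed.

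**What to change.** **Statistical Analysis.** Add a bootstrap of the whole procedure, with at least 1,000 resamples. In each, compute the 12 odds ratios and lower limits, pick the winner, and compare that score's log odds ratio, c-index and positive predictive value in the resample with its values in the original data. The mean difference estimates the optimism and is subtracted from the winner's apparent values. Report adjusted and apparent values side by side, and how often each score wins. State that the adjustment is approximate: it can under-correct when scores are similar and over-correct when one dominates.

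**Discussion.** Replace the word *validated* by a statement that the score was selected in one single-centre cohort and needs external confirmation before it is relied on.

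**Cost.** A short script in R, which the plan already names, and a few sentences of text. No new patients or data are needed. The winner's reported performance will look less favourable.
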